## IV. a. 2. Justification of Study Design

IV. a. 2. Justification for a pragmatic design: Pragmatic, or naturalistic designs, are designed to evaluate how a technology works in normal or usual practice and take into account patient and provider variations and can range from experimental to quasi-experimental studies. Pragmatic experimental designs retain random allocation to treatments to minimize bias, but offer fewer restrictions in how patients are recruited and followed after randomization, thus increasing external validity and generalizability. Pragmatic experimental designs have been used previously to evaluate strategies to promote the adoption of low-risk public health recommendations, such as CMS's evaluation of the Health Support pilot (i.e., Chronic Care Improvement Program) or the National Health Service's (NHS) evaluation of the impact of fecal occult blood test (FOBT) screening for colorectal cancer.

Generally, experimental designs are structured so that recruitment precedes randomization in order to evaluate the efficacy of an intervention; however, randomization occurs before recruitment (i.e., enrollment) in pragmatic methodologies which are designed to evaluate the effectiveness of an intervention. The use of the pragmatic design balances the goals of internal and external validity.

IV. a. 3. Sample Size: The study was powered for acute inpatient admissions, the most restrictive outcome, using the sample size estimation for trials of recurrent events in SAS. A baseline study of patients meeting the high-need, high-cost criteria suggests that a total sample size of 171,454 (85,727 per treatment arm) would provide the study with  $\geq 80\%$  power to detect the following intent to treat differences between treatment groups at an  $\alpha=0.05$  over the first 12 months of the four year study:

- a 2.5% reduction in acute inpatient admissions
- a 2.5% reduction in 30-day all-cause readmissions
- a 2.5% reduction in emergency room visits
- a 2.5% increase in primary care physician visits
- a 2.5% increase in specialist physician visits

Given a treatment effect of a 20% reduction in utilization for the as-treated population, an average of 10.6 months of at-risk exposure, an estimated program engagement rate of 20% of the qualified population with an average of 6.5 months of engagement in the program, a sample size of 85,727 individuals in the program treatment arm was used to power the most restrictive outcome (i.e., acute inpatient admissions) using preliminary data. In other words, the study's original planned sample size of approximately 200,000 members for the initial 12-month period, including both treatment arms, was sufficient to allow decision makers to assess if the CM/CC intervention could improve the targeted outcomes in the qualified population by year. The larger

cumulative sample sizes, included in years 2-4 of the study also address the salient business need for continuous quality improvement – the foundation of a QIS.

IV. a. 4. Rationale for the study endpoint: The study endpoint is defined as documentation of utilization including acute inpatient admissions, 30-day all-cause re-admissions, outpatient emergency room (ER) visits, primary care physician (PCP) visits, and specialist physician visits using administrative claims data. These outcome measures align with National Committee on Quality Assurance's (NCQA) Healthcare Effectiveness Data and Information Set (HEDIS) quality measures, Centers for Medicare & Medicaid Services' (CMS) Five Star Quality Rating System for Medicare Advantage Plans, and prior analysis of the effectiveness of care coordination and case management programs, represent significant costs and indicators of complications as well as represent important factors needing additional research as it relates to the care of patients.

IV. a. 5. Justification for using administrative data: Access to and analysis of medical, behavioral, and pharmacy claims and notification data, including diagnosis codes, revenue codes and procedure code level detail is required to summarize, compare and document appropriate inclusion and exclusion criteria are met as well as utilization rates including inpatient admissions, emergency room visits and physician visits for the purpose of determining the effectiveness of the CM/CC program. The use of this administrative data aligns with methods used in published reports (e.g., HEDIS and Five Star) on outcomes and research conducted on care coordination and case management program outcomes.

IV. a. 6. Study limitations and alternative design

The primary limitation of the proposed study design is related to misclassification of high-need, high-cost status (i.e., identification in the top five percent of spend and utilization in the previous year and in the next 12 months) based on the prospective, proprietary administrative algorithm. This limitation could be addressed via the expansion of the current study to include outreach for all members in the top five percent of spend and utilization in the previous year. In prior comparative validity studies (N= 149,011), the use of all members in the top five percent of spend and utilization in the previous year as a predictor of top five percent of spend and utilization in the next 12 months resulted in a sensitivity of 100% and a PPV of 36%. However, the application of this alternative design has a significant financial burden since only 36% of members in the top 5% of cost in the previous year prospectively remain in the top 5% in the next year. The identification and stratification of qualified members is a critical component of the success of the program. With any case management program, cost effective allocation of limited case management resources can only be achieved if organizations can identify a small number of high-risk members with low false positive rates. While the sensitivity and specificity of the predictive models are important, positive predictive validity (PPV) must be the primary focus. The prospective score allows for the identification of a smaller number of individuals with a higher sensitivity and higher PPV; thereby, allowing for the cost effective allocation of limited CM/CC resources. The same argument for the cost-effective allocation of limited resources applies to the new high inpatient risk algorithms.

The second limitation of the proposed study design relates to the following three scenarios where the control population may receive CM/CC: 1) the member is identified as being at high risk for readmission upon discharge from the hospital, 2) the member is directly referred to the program by their physician, or 3) the member self-refers to the program. Based on an April 2015 baseline study, it was estimated that this issue will only impact 5-10% of the control group. These two scenarios will result in some "contamination" of the effect in the control group resulting in the lack of a "pure" control group to determine program impact. Participants in both treatment arms are receiving differing levels of the intervention. This limitation could be addressed by limiting care coordination and/or case management to the intervention population. However, this would deprive members who are facing an imminent health situation (either a high-risk discharge or physician determined risk) from receiving the Stage 1 program. Furthermore, both treatment arms also have access to other care or disease management programs, for conditions such as cancer, chronic kidney disease, end-stage kidney disease, or organ transplant.

A third consideration is related to the evolving nature of the care coordination and case management program that will be delivered to members during the course of the study. As a part of continuous quality improvement, the program team may make changes to materials and interventions, and additional interventions may be added. The research team will assess the magnitude of any operational or clinical changes and appropriately inform the review board using established procedures.

Lastly, the proposed QIS was designed as a pragmatic study to evaluate the comparative effectiveness of two low-risk public health approaches to deploy the CM/CC program as they occur in natural settings. The goal of the study is to identify the optimal “real world” approach so that it can be leveraged across the entire population. As such, the QIS could not practicably be carried out without a waiver of informed consent. While a more general experimental design (recruitment followed by randomization) would allow for the documentation of informed consent for all participants, this design would also have external validity concerns. Furthermore, individuals in both treatment arms will receive the CM/CC intervention if they meet the criteria highlighted in the second limitation.

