#### **IV. b. Data Analysis and Data Monitoring**

*Primary Data Analysis:* All analyses will be based on administrative data. In order to address claims lag, the administrative data will be pulled four months following the end of each intervention period.

Univariate analyses (standardized differences) will be used to test for baseline differences between the treatment groups. Any statistically significant differences in baseline characteristics will be controlled for in the multivariable models assessing the study outcomes. Unless otherwise noted, all tests will be two-sided tests with  $\alpha = 0.05$ . Model diagnostics will be utilized to evaluate the need to address outliers.

The primary study outcomes include the following:

- a 2.5% reduction in acute inpatient admissions
- a 2.5% reduction in 30-day all-cause readmissions
- a 2.5% reduction in emergency room visits
- a 2.5% increase in primary care physician visits
- a 2.5% increase in specialist physician visits

Utilization metrics will be compared between intervention groups at 12, 24, 36 and 48 months following randomization using a repeated measures Poisson or negative binomial regression model. Zero-inflated models will be utilized if appropriate. The Cox proportional hazards test will be used for all cause 30-day readmission. Results will be reported in aggregate, as well as stratified by year of randomization.

*Secondary Data Analyses:* The study will also explore numerous secondary outcomes that were not powered, but that are important for continuous quality improvement – the primary goal of a QIS. Examples include the following:

- Total cost of care: Utilization and cost will be evaluated for all service categories to identify hypotheses for continuous quality improvement.
- Variable cohort definitions:
  - A “once qualified, always qualified” definition will be used to evaluate the long-term impacts of the program after a member is no longer identified by the monthly refresh of the algorithms. This mirrors a more academic approach to the measurement of outcomes.
  - An “operational” definition will include members until 120 days after they are no longer actively identified by the monthly refresh of the algorithms. This view is designed to drive continuous quality improvement.
- Health plan type: The impact of the program among the Individual Exchange population compared to the traditional Fully Insured population will be evaluated.

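### At least 80% power for a 2.5% reduction in 30-day readmissions does not follow from a sample size solved on admissions, and admissions are not the most restrictive of the five outcomes

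*Protocol*

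**What the plan says.** Protocol section IV.a.3 (Sample Size) says "The study was powered for acute inpatient admissions, the most restrictive outcome", "using the sample size estimation for trials of recurrent events in SAS". It then says that "a total sample size of 171,454 (85,727 per treatment arm) would provide the study with" at least 80% "power to detect the following intent to treat differences between treatment groups at an" alpha of 0.05 over the first 12 months of the four-year study. Five differences follow, among them "a 2.5% reduction in acute inpatient admissions" and "a 2.5% reduction in 30-day all-cause readmissions". A later paragraph of the same section again describes admissions as the most restrictive outcome and gives about 200,000 members as the planned first-year enrolment.

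Section IV.b lists both outcomes as primary, states that "all tests will be two-sided tests with" alpha 0.05 unless otherwise noted, and assigns a Cox model to readmission. The protocol gives no admission rate, no readmission rate, no dispersion and no separate calculation for readmissions.

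**The concern.** A 30-day readmission is an admission that follows an earlier discharge. Counted in the same members, there must be fewer readmissions than admissions. For a fixed relative effect, precision depends on the number of events, so the rarer outcome needs more members. Of these two outcomes, readmission should therefore be the binding one, and the protocol has the order reversed.

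At stake is how the first-year result is read. Section IV.a.3 tells decision makers that the sample is large enough to assess the targeted outcomes by year. A null readmission result taken to come from a comparison with 80% power would look like evidence against an effect, when the comparison may have had a small chance of detecting it.

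**Working it through.** **Inputs from the protocol.** 85,727 per arm, 1:1; power 80%; two-sided alpha 0.05; ratio 0.975 for both outcomes (sections IV.a.3 and IV.b). Also from IV.a.3: 20% as-treated effect, 20% engagement, 6.5 months engaged out of 10.6 months at risk.

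**Inputs not given, so assumed.** The share f of admissions that are 30-day readmissions: 10% to 30%. The dispersion k: from 0 (Poisson) upwards. The admission rate is solved back from the sample size.

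**Step 1: the effect reproduces.** 0.20 × 0.20 × 6.5/10.6 = 2.45%, or about 2.5%.

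**Step 2: what the sample size implies for admissions.** The recurrent-event formula per arm is n = (1.960 + 0.842)² × (1/μ0 + 1/μ1 + 2k) / (ln 0.975)², with μ1 = 0.975 μ0. The sample size cannot be reproduced forward, because μ0 and k are not stated. Solved backward, 1/μ0 + 1/μ1 + 2k = 85,727 × 0.000641 / 7.849 = 7.00. With k = 0, μ0 = 0.289 admissions per member over 10.6 months. Total admissions are then 85,727 × 0.2893 × 1.975, or about 48,990.

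**Step 3: events needed for readmissions.** For a Cox comparison (Schoenfeld), events = 4 × 7.849 / (ln 0.975)² = 31.4 / 0.000641, or about 48,980. In the Poisson case practically every admission would have to be a readmission.

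**Step 4: readmission power, Poisson case.** Power = Φ(√(events/4) × 0.0253 − 1.960), with events = f × 48,990. Multiplying events by 200,000/171,454 gives the fourth column. The last column is 85,727/f.

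| f | Events | Power, 171,454 members | Power, 200,000 members | N per arm for 80% |
|---|---|---|---|---|
| 10% | 4,899 | 14% | 16% | 857,270 |
| 20% | 9,797 | 24% | 27% | 428,635 |
| 30% | 14,696 | 34% | 38% | 285,757 |

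The reduction detectable with 80% power, 1 − exp(−√(31.4/events)), is about 7.7%, 5.5% and 4.5% for these three rows.

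**Step 5: readmission per index discharge.** Comparing proportions f and 0.975f with 85,727 × 0.2893, or about 24,800, discharges per arm gives 15% power at f = 10% and 45% at f = 30%. About 80% is reached only near f = 50%.

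**Step 6: overdispersed counts.** A larger k allows a higher admission rate for the same sample size. The variance of the log ratio for readmissions is [(1/μ0 + 1/μ1)/f + 2k_R] / 85,727, where k_R is the readmission dispersion.

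| k for admissions | Implied μ0 | Power, k_R = k, f = 10% to 30% | Power, k_R = 0, f = 10% to 30% |
|---|---|---|---|
| 1 | 0.41 | 18% to 40% | 18% to 44% |
| 2 | 0.67 | 24% to 51% | 27% to 65% |
| 2.5 | 1.01 | 32% to 58% | 38% to 82% |
| 2.8 | 1.45 | 39% to 64% | 51% to 93% |

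With equal dispersion, power stays between about 18% and 64%. It reaches 80% only in the last column, at about one or more admissions per member and with the larger shares.

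**The case against.** The strongest objection is that the rates behind the calculation sit in a baseline study that the protocol does not reproduce. The cohort is selected for high spend, so an admission rate near or above one per member cannot be ruled out. With k about 2.5 or more for admissions and no overdispersion in readmissions, 80% is attainable. This stands: a reader might infer that the stated power is impossible, and the document does not support going that far. Such a combination is hard to reconcile with readmissions clustering within members, but that is a judgement, not a figure in the protocol.

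A reader might also infer that power falls further because controls also receive the program where "the member is identified as being at high risk for readmission upon discharge from the hospital". It does not. The claim concerns a fixed 2.5% intent-to-treat difference, and power at a fixed difference is unaffected by control access. Access bears on whether 2.5% is achievable, a separate question, and section IV.a.6 already discloses it as affecting an estimated 5% to 10% of controls.

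The strict subset relation is itself an inference, since the protocol does not say which admissions count as readmissions or whether the Cox model runs per member or per discharge. Step 5 shows that the per-discharge reading does not remove the shortfall over the assumed range.

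Finally, about 705,000 members are to be randomised over four years, and outcomes are also compared at 24, 36 and 48 months. That softens the consequence for the aggregate analysis. Under Poisson counts and 1:1 allocation, 705,000 members reach 80% once f is about 24% or more. It does not rescue a statement made for 171,454 members over the first 12 months.

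**Conclusion.** The point holds as a flaw in the stated power. Admissions are not shown to be the most restrictive outcome, and at least 80% power for a 2.5% readmission reduction does not follow from the sizing. The likely power is about 14% to 34% under Poisson counts and about 18% to 64% with equal overdispersion (k = 1 to 2.8).

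This rests on three assumptions: that 85,727 was solved for about 80% on admissions, as the unrounded figure and the wording indicate; that 10% to 30% of admissions are readmissions; and that readmissions are not far less overdispersed than admissions. The size of the shortfall depends on the assumed share. Its direction does not, outside the one exception described above. The sizing for admissions is not in question.

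**What to change.** In both places in section IV.a.3, delete the description of admissions as the most restrictive outcome. From the baseline study, state the readmission rate and dispersion, and compute either the power for a 2.5% reduction or the reduction detectable with 80% power under the planned Cox analysis. Limit the 12-month claim of at least 80% power to the outcomes that meet it.

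Readmissions may stay a primary outcome with their actual power stated; low power alone does not require demoting them. The cost is a wording change and one recalculation from data that the sponsor should already hold. Randomisation, data collection and the analysis models are untouched.

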The CHW tracked the status of all scheduled home visit attempts. In the case of an unsuccessful home visit, the CHW made three call attempts to reschedule the home visit. A field visit was attempted on members who were unable to be reached by phone by the CHW. During the home visit, the CHW completed the Access to Care questionnaire and the PHQ-9 survey. The information documented by the CHW included but was not limited to: primary care physician visits, transportation needs, medication concerns, and home health and durable medical equipment needs. If the member was recently hospitalized, the CHW completed the Post Hospitalization assessment.

If during the initial outreach call by the CHW, it was determined that the member was not within the service area, or if member refused a home visit, but agreed to talk over the phone, the CHW completed the Access to Care questionnaire and the PHQ-9 survey during the initial outreach call. If the member was not able to talk immediately, a follow-up telephone call was scheduled to continue the conversation.

During subsequent telephonic contact with the Community Care Team clinicians, the assigned RN may have also completed the Adult Core assessment or the SF-12 survey based on clinician judgment. Members were managed longitudinally until three months after they were no longer identified as eligible for the program.

**Control Group:** It is important to note that throughout the study period, the CM/CC program will continue to be available to all commercial health plan members (including the control group in the current QIS) who are 1) discharged from an inpatient facility and identified as being at high risk for readmission and 2) identified via physician referral or self-referral as someone who may benefit from care coordination. It is expected that approximately 5-10% of the 100,000 members randomized to the control group will receive the CM/CC intervention. Furthermore, engagement in other programs will be monitored in order to determine if stratification is necessary since both treatment arms also have access to other care or disease management programs, such as Transplant Resource Services, the End Stage Renal Disease program, the Chronic Kidney Disease program, the Cancer Support program, or the Heart Failure Disease Management program.

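### The 2.5% planning difference and the year-1 power claim leave no room for programme use in the control arm, although the protocol expects 5-10% of controls to receive CM/CC

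*Protocol*

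**What the plan says.** Section IV. a. 3 (Sample Size) states that "a total sample size of 171,454 (85,727 per treatment arm) would provide the study with" at least 80% power at alpha 0.05 over the first 12 months. The first listed difference is "a 2.5% reduction in acute inpatient admissions", described as an intent-to-treat difference. Section IV. b sets the sidedness: "Unless otherwise noted, all tests will be two-sided tests with" alpha 0.05.

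The inputs follow in IV. a. 3: a 20% reduction in the as-treated population, 10.6 months of at-risk exposure on average, and "an estimated program engagement rate of 20% of the qualified population with an average of 6.5 months of engagement in the program". No control-arm uptake is listed. The same section calls the originally planned year-1 enrolment of about 200,000 members sufficient for decision makers.

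Three other places describe programme use among controls:
- IV. a. 8 (Control Group): "It is expected that approximately 5-10% of the 100,000 members randomized to the control group will receive the CM/CC intervention".
- IV. a. 6 (limitations), citing an April 2015 baseline study: "it was estimated that this issue will only impact 5-10% of the control group". It calls this contamination.
- IV. a. 1 (Overall Strategy): the primary hypothesis describes the 5-10% as members who qualify, not members who receive the programme.

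**The concern.** An intent-to-treat difference depends on the contrast in programme use between the arms. The stated inputs reproduce the 2.5% with the control arm's share set to zero, whereas the protocol expects a non-zero share and had an estimate of it from its own baseline study. The contamination is disclosed as a limitation but is not carried into the effect size or the power.

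This matters for year 1 in particular. IV. a. 3 offers the 12-month sample as enough for a decision by year, and IV. b plans results stratified by year of randomization. If true power is well below 80%, a programme that works as assumed could easily miss significance in year 1 and be judged ineffective.

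**Working it through.** **1. Reproduce the planning effect.** As-treated effect x engagement x share of at-risk time engaged = 0.20 x 0.20 x 6.5/10.6 = 0.0245. This rounds to the stated 2.5%. Without the time factor it would be 4.0%, so the time factor was evidently used. No control term is needed to reach the figure. Zero control uptake is therefore inferred from the arithmetic; the protocol does not state it.

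**2. Calibrate the precision.** The baseline admission rate and dispersion are not given, so 85,727 cannot be rebuilt independently. I take 85,727 per arm to give exactly 80% power at a rate ratio (RR) of 0.975, two-sided 0.05. The standard error of log RR is then |ln 0.975| / (1.960 + 0.842) = 0.02532/2.8016 = 0.009037. At 100,000 per arm it is 0.009037 x sqrt(85,727/100,000) = 0.008367.

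**3. Add control uptake.** With shares t and c treated in the intervention and control arms, and equal effect and duration, the coefficient is 0.20 x 6.5/10.6 = 0.12264, so RR = (1 - 0.12264t)/(1 - 0.12264c). Power = Phi(|ln RR|/SE - 1.960).
- t = 20%, c = 5%: RR = 0.97547/0.99387 = 0.98149, |ln RR| = 0.018683, power = Phi(2.067 - 1.960) = 54%.
- t = 20%, c = 10%: RR = 0.97547/0.98774 = 0.98758, |ln RR| = 0.012494, power = Phi(1.383 - 1.960) = 28%.

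To regain 80%, n per arm = 85,727 x (ln 0.975/ln RR)^2, about 157,400 (5%) and 352,000 (10%).

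**4. Other readings of the same text**, on the same calibration:

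| Reading | Treated, intervention vs control | Reduction | Power at 171,454 | Power at 200,000 |
|---|---|---|---|---|
| 20% is total uptake; controls engaged 6.5 months | 20% vs 5% | 1.85% | 54% | 61% |
| | 20% vs 10% | 1.24% | 28% | 32% |
| Same, controls engaged half as long (3.25 months) | 20% vs 5% | 2.15% | 67% | 74% |
| | 20% vs 10% | 1.85% | 54% | 61% |
| Same, controls engaged 2 months | 20% vs 5% | 2.27% | 72% | 78% |
| | 20% vs 10% | 2.08% | 64% | 71% |
| 5-10% only qualify; 20% of those engage | 20% vs 1% | 2.33% | 74% | 81% |
| | 20% vs 2% | 2.21% | 70% | 76% |
| 20% is on top of standard referral, chance overlap | 24% vs 5% | 2.34% | 75% | 81% |
| | 28% vs 10% | 2.23% | 71% | 77% |
| 20% is on top of standard referral, no overlap | 25% vs 5% | 2.47% | 79.0% | 85% |
| | 30% vs 10% | 2.48% | 79.5% | 85% |

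For shorter control engagement, the control coefficient is 0.20 x months/10.6. The chance-overlap shares are 0.20 + c - 0.20c.

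**5. Cumulative sample.** With 705,000 split equally (352,500 per arm), the first reading gives 98.7% (5%) and 80.1% (10%). A 40/60 split throughout inflates the variance by (1/0.4 + 1/0.6)/4 = 1.042, giving 98.4% and 78.4%. The actual split was 50/50 until 10/01/2017, so the 10% case lies between 78% and 80%.

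**The case against.** A reader might infer that year-1 power simply is 28-54%. The protocol does not support that as an unconditional figure, for four reasons.

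- **What the 20% covers.** Subtracting 5-10 points requires the 20% to be all programme use in the intervention arm, including standard referrals, which stay open to both arms. The protocol does not say this. The original capacity in IV. a. 8, about 20,000 members a year, is 20% of a 100,000-member arm and so fits a gross rate. However, about 30,000 members already took part in 2014, which makes it hard to see that capacity as covering standard referrals too. If the 20% comes on top of standard referral, most of the loss disappears.
- **Duration in controls.** Controls enter through a discharge or a referral. The Background describes care coordination as usually short-term, and the Stage 2 text gives Stage 1 about 60 days. Equal engagement of 6.5 months is an assumption.
- **Qualified or received.** The primary hypothesis uses the weaker word. IV. a. 8 plainly says receive, and IV. a. 6 speaks of impact on that share, so receipt is the more natural reading, but the passages differ.
- **Sample and calibration.** The sufficiency claim refers to about 200,000 members, not 171,454, and the protocol says at least 80%, not exactly 80%. A higher true starting power would raise every figure.

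All four stand as reasons to make the range conditional. They do not remove the point: the control uptake is absent from the stated inputs, and disclosing contamination as a limitation does not correct a power figure that ignores it.

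**Conclusion.** The point holds in conditional form. The 2.5% matches the listed inputs only with no programme use among controls, contrary to the protocol's own expectation. If the 20% is total intervention-arm uptake and treated controls get the same effect and duration, the expected difference is about 1.2-1.9%, with year-1 power of about 28-54% at 171,454 and 32-61% at about 200,000.

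At 171,454, every reading tested falls below 80%. When standard referral adds equally to both arms the shortfall is trivial (79.0-79.5%) and comes from rounding 2.45% up to 2.5%. At about 200,000, some of the milder readings reach or pass 80%.

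Nor does it follow that the trial as a whole is underpowered. On the least favourable reading the cumulative sample gives roughly 78-99%. That assumes later members resemble the planning population and contribute information at the year-1 rate. Inpatient referrals engaged from 09/01/2018 may differ, and the 10% case has no margin.

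**What to change.** In IV. a. 3:
- State the assumed control-arm uptake and engagement duration, and whether the 20% engagement includes standard referrals.
- Reconcile the 5-10% who qualify in IV. a. 1 with the 5-10% who receive the programme in IV. a. 8.
- Recompute the net intent-to-treat difference and restate year-1 power for acute inpatient admissions at 171,454 and at about 200,000, with a range over the assumptions that remain uncertain.
- Replace the unqualified claim that the 12-month sample was sufficient with the restated power. Name the planned cumulative sample of about 705,000 as the better-powered analysis, with its power allowing for the 40/60 allocation.

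The cost is one recalculation and revised wording. No endpoint, analysis or enrolment target changes. The only downside is a less favourable stated year-1 power.
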